## Abstract

**Background:**

Benign prostatic hyperplasia (BPH) and its associated lower urinary tract symptoms (LUTS) occur very commonly in older men. BPH and LUTS cause substantial physical and psychological impairment that could seriously affect the quality of late life and greatly cost the health-care systems. Current surgical and pharmacological therapies are expensive, may not effectively improve prostate function and health but cause adverse effects. There is an urgent need to find new and effective non-pharmacological preventions and treatments. Yi Jin Jing and Tai Chi are two common traditional Chinese mind–body exercises with different movements and techniques, but both emphasize regulating functional homeostasis and keeping whole body harmony. Yi Jin Jing and Tai Chi have not been studied much for potentially use in the treatment of BPH-related problems. The primary purpose of this protocol is to assess the effectiveness of Yi Jin Jing versus Tai Chi on the monographic and functional changes of prostate in older men.

**Methods/Design:**

A prospective single-center randomized controlled trial will be conducted. A total of 150 old men (60–70 years old) will be recruited from the urban tertiary of Shanghai, China. Of these, 50 eligible participants will be randomly assigned to a control group and two intervention groups with either Yi Jin Jing or Tai Chi exercise training. They will undergo 30 minutes for each exercise for five times a week for 6 months. The primary outcomes are changes of signs and symptoms in BPH and lower urinary tract from baseline to post-intervention. The main secondary outcomes are exercise-induced effects on the circulating levels of estrogen and androgen. All the outcome measures will be assessed at baseline, immediately after the 6-month intervention, and at the 3-month post-intervention follow-up.

**Discussion:**

This proposed study will be the first comparative randomized clinical trial to evaluate the effectiveness of Yi Jin Jing versus Tai Chi exercise on prostate health among older adults. The results will provide an evidence-based recommendation for Chinese older men on the use of Yi Jin Jing and Tai Chi training to promote prostatic function and health. Potential mechanisms for the regulatory effect of the two exercises elucidated by multiple outcomes are also explored. A clarification of the effects and mechanisms may provide information for the development of new strategies in the prevention and treatment of BPH-related conditions.

**Trial registration:**

ClinicalTrials.gov Identifier: ChiCTR-IOR-16007698. This trial was registered on 4 January 2016.

## Background

Known as a benign and non-cancerous enlargement of the prostate gland, benign prostatic hyperplasia (BPH) with its associated lower urinary tract symptoms (LUTS) is extremely common among male individuals. The number of BPH patients increases each year and it has become one of the major health concerns. The prevalence of BPH is highly correlated with age and thus, BPH-related conditions occur more commonly among older males [1–3]. Recent statistics from China, for example, have shown that an estimated 62.9 % of men over the age of 50 have been diagnosed with BPH in Pudong New District of Shanghai. The prevalence of BPH may accelerate with aging, and the incidence can increase to 73.9 % and 84.2 % of older individuals in their seventh and eighth decades, respectively [4]. BPH interferes with the normal flow of urine and leads to many LUTS, including urinary hesitancy, frequent urination, urgency, thin urine flow, and urinary retention [5–7]. As a result, BPH can greatly affect the patients’ physical and mental health and have devastating effects on quality of life, plus there is loss of productivity and increased health-care costs.

Fast emerging as a major public health concern, scientific research on the prevention and treatment of BPH has become critical and has attracted significant attention, particularly for older men. However, the causes of BPH are complex and the overgrowth of the prostate gland is multifaceted involving various factors such as aging, hormones, late activation of cell growth, genetic, and lifestyle elements [8, 9]. Benefits have been found for current BPH treatment options including medication, minimally invasive therapies, and prostate surgery with continued surveillance [3, 10]. Unfortunately, current surgical and pharmacological therapies have limitations. For example, the drugs and surgeries are expensive, may not effectively improve prostate function and health, and may carry a hidden cost of significant risk of serious adverse events. Thus, there is an urgent need to find new and effective non-pharmacological preventions and treatments for individuals, especially older adults, with and without BPH and associated LUTS.

Importantly, accumulating evidence indicates that the development and progression of BPH and prostate cancer are closely related to a sedentary lifestyle. For example, the incidence of prostate cancer can be reduced by physical activity (PA) and exercise training [11–14]. More physically active men have a lower frequency of BPH and associated LUTS [15–17]. Occupational PA is inversely associated with BPH [18]. Exercise can effectively reduce the risks of symptomatic BPH and LUTS [19].

As a common and important mind–body (MB) exercise, Tai Chi interventions have been reported as having effective influence on health problems and chronic diseases, including fibromyalgia [20], type-2 diabetes mellitus [21], stroke [22], knee osteoarthritis [23], Parkinson’s disease [24–26], chronic obstructive pulmonary disease [27, 28], and BPH [29, 30]. There has not, however, been much research on Tai Chi training and BPH with associated LUTS. Only one randomized controlled trial, to our knowledge, has tried studying the topic [29]. This short-term study suggests that 12-week Tai Chi training may improve LUTS and quality of life in elderly patients with BPH, but the limitations and difficulties encountered in this study elicit a significant need for more prospective clinical trials.

Like Tai Chi, Yi Jin Jing is an attractive traditional Chinese MB exercise that is quickly emerging in China and is getting more and more attention due to its effects on health and physical fitness [31–33]. In recent years, Yi Jin Jing exercise training has been widely applied to improve physical functions, to promote health, and to prevent or treat disease-related conditions and physical disabilities. Some reported benefits of Yi Jin Jing practice include enhanced dynamic nervous response speed [34]; decreased Quetelet index and improved lung capacity [35]; improved body serum superoxide dismutase activity and decreased serum malondialdehyde (MDA) levels [36, 37]; delaying the decline of intelligence by improving thinking agility, action time, and short-term memory [38]; and improvements of psychological adjustment capability and depression [39–41].

To our knowledge, no research has been conducted on Yi Jin Jing training, BPH and its associated LUTS. The preliminary results of our pilot study on rat models presented a three-dimensional relationship between androgen levels and prostate volume [42]. However, the relationship for the role and effect of Yi Jin Jing training in mediating hormone regulation is not known. It is still unclear if this type of exercise provides health benefits that will prevent BPH and is therapeutic for patients with BPH and LUTS. Accordingly, we designed this randomly controlled trial with the specific purpose of investigating the effectiveness of a 6-month Yi Jin Jing exercise program on prostate function and health in older individuals, determining the direction and magnitude of Yi Jin Jing exercise-induced changes (including secretion of the sex hormone androgen and prostate volume), and exploring the molecular mechanisms that mediate these effects of Yi Jin Jing exercise on BPH.

## Methods/Design

### Study design

To examine the effectiveness of the Yi Jin Jing exercise intervention on older adults, compared with Tai Chi training, we designed this study as a single-center repeated-measures randomized controlled clinical trial. Old subjects will be recruited from the community of Shanghai, China. With a 1:1:1 allocation ratio, enrolled eligible volunteers will be randomly assigned to three parallel arms including two intervention groups and a non-intervention control group (*n* = 50 per group). Participants in the two intervention groups will train with Yi Jin Jing or Tai Chi exercise continually for 6 months, while the control group will not receive any intervention. Assessments of the primary and secondary outcomes and data analysis will be performed at baseline, immediately after the 6-month intervention, and at the 3-month post-intervention follow-up. All tests and measurements will be conducted by trained professionals who are blinded to the group assignment of subjects and their specific background. The flow of participants through the trial is shown in Fig. 1.

**Fig. 1 Fig1:**
[figure not shown]
Study design as flow diagram: recruitment, randomization, intervention, follow-up, assessment, and outcomes

### Sample size

The sample size was estimated using a randomized controlled trial about Tai Chi for LUTS and BPH [29] and we expanded the sample size to make it adequate to detect the expected changes of prostate volume. Ultrasound will be used to measure these changes before and immediately after the 6 months of Yi Jin Jing exercise training, and at the 3-month post-intervention follow-up. It is estimated that a sample size of 40 participants per group will be required to observe a similar result with a power of 80 %. Considering a 20 % dropout and exit rate, we will recruit 150 subjects with 50 in each group.

### Participant recruitment and selection

Participants are recruited by word of mouth, flyers, email lists, organization or club meetings, and other relevant activities from the general population in Shanghai, China. The first step is to use an interview to recruit the potential older individuals who are interested in participation in the research. Potential participants 60–70 years old are invited and screened using a RAND-36 questionnaire [43, 44]. After completing the questionnaire screening, the interested and eligible participants are asked to attend an information meeting. They are provided with a written informed consent form to be signed and they continue with the further steps, beginning with a more detailed health screening and physical assessment.

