### Inclusion criteria

Participants are required to meet all the following criteria:Aged between 60 and 70 yearsA relatively stable body weight over the past 6 months with a weight change of less than 2 %A sedentary lifestyle, not having exercised for the past 3 months, or exercising occasionally less than once a week for 20 min each timeNo Yi Jin Jing and/or Tai Chi training experience for the past 3 monthsApparently healthy, free of cardiovascular disease, and not being treated with BPH drugs or other therapies during the last 6 monthsVoluntary participation in this research for at least 6 months and provision of written informed consent

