To the best of our knowledge, this is the first study to evaluate the effectiveness of Yi Jin Jing versus Tai Chi training on prostate function and health in a large older population. This trial will determine the effects of a 6-month Yi Jin Jing training program on adaptive changes of the prostate, including anthropometric, physiological, and biochemical parameters, in older men. We will also compare Yi Jin Jing and Tai Chi, as two important MB exercises, regarding their preventive and/or therapeutic benefits on prostate health. This trial will evaluate monographic and functional changes induced in the prostate by Yi Jin Jing and Tai Chi through monitoring a wide spectrum of health indices, including blood pressure, blood serum biochemical test, hematology indices of sex hormones (estradiol, testosterone, double hydrogen, and androgen), and an ultrasound of the prostate. Thus, the measured and analyzed data will allow us to explore possible cellular and molecular mechanisms that mediate these effects of Yi Jin Jing compared to Tai Chi on BPH, such as by examining the corresponding changes in sex hormones levels and through an advanced analysis of the serum E_2_/T ratio, a mathematical simulation of serum E_2_/T ratio, and the prostate viscera coefficient. Importantly, no studies have considered if long-term and short-term interventions of Yi Jin Jing versus Tai Chi exercise have a different role in mediating the hormone regulatory effect on BPH. Accordingly, we are expecting to learn whether participants receiving different periods of supervised Yi Jin Jing and Tai Chi training (12 weeks, 24 weeks, and 36 weeks) have different improvements in the biomarkers measured.

Successful completion of the proposed study will contribute to the evidence-based knowledge of whether Yi Jin Jing and Tai Chi are clinically favorable and preferable as simple, inexpensive, effective, and durable prevention and/or treatment approaches for the major disabling disease BPH, which incidentally may decrease the economic costs to the health-care system. The results of this study may provide valuable information for the development of new strategies in preventing and/or treating BPH and the associated LUTS and thus, they may have important public health implications for older adults with/without such chronic conditions.

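### Baseline symptom status has no stated part in entry, randomisation or analysis, so pooled IPSS and Qol effects may be diluted and would not by themselves support a BPH treatment statement

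*Protocol article*

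**What the plan says.** Under Participant recruitment and selection, men are sought through several community routes and "other relevant activities from the general population in Shanghai, China". Those aged 60 to 70 "are invited and screened using a RAND-36 questionnaire". After consent they go on to further steps, "beginning with a more detailed health screening and physical assessment", whose content is not described.

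The Inclusion criteria open with "Participants are required to meet all the following criteria". The only one that touches the prostate is negative: entrants must be apparently healthy, "free of cardiovascular disease, and not being treated with BPH drugs or other therapies" in the previous 6 months. The Exclusion criteria add nothing on urinary symptoms or prostate status.

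The Abstract puts the endpoint this way: "The primary outcomes are changes of signs and symptoms in BPH and lower urinary tract from baseline to post-intervention". Study outcomes lists three primary outcomes: prostate volume, IPSS and urination-related Qol.

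On size, "The sample size was estimated using a randomized controlled trial about Tai Chi for LUTS and BPH", with an expansion said to make the number adequate for prostate volume. The Background describes that earlier trial as one in elderly patients with BPH.

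The end of the Background asks whether Yi Jin Jing prevents BPH and also whether it helps patients who have BPH and LUTS. The Discussion hopes to learn whether the exercises are "effective, and durable prevention and/or treatment approaches for the major disabling disease BPH". The Background and the Discussion both say that men with and without the condition are of interest.

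**The concern.** IPSS and urinary Qol are burden scores with a best possible value. A man who enters at or near that value can worsen or stay the same, but he can hardly improve. If the arms mix such men with symptomatic men, the difference in mean change averages a possible effect with a near-zero one.

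Two things are at stake. A null result on IPSS or Qol could mean that the exercises do not work, or that too few men had symptoms to relieve. A favourable pooled result would describe older men in general and would not on its own say what happens in men with BPH, which is what a treatment statement needs. The planning trial adds to this, because its result came from patients with BPH and is carried over to a community sample described as apparently healthy.

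**Working it through.** **1. The plan's own figure.** Inputs from Sample size: 40 per group, 80 % power, 20 % dropout.
- 40 / (1 − 0.20) = 50 per group, and 3 × 50 = 150. The dropout step reproduces.
- The 40 cannot be reproduced, since no effect or SD is given. Working backwards with two-sided alpha 0.05 (the protocol gives 0.05 but not the sidedness) and a two-group comparison of means: d = √(2/40) × (1.960 + 0.842) = 0.626.

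**2. Where baseline status could enter the design.**

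| Section | Role of baseline symptoms or prostate status |
|---|---|
| Recruitment and selection | None stated; further screening has no described content |
| Inclusion and exclusion criteria | None, apart from no recent BPH treatment |
| Randomization | Equal groups by computer after consent; no stratification stated |
| Statistical analysis | Repeated-measures ANOVA and Mann-Whitney tests; no analysis by baseline status stated |

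**3. Dilution, as an illustration.** Let p be the share of men who can improve, and suppose the rest change by zero on average. Then

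mean effect = p × (effect in affected men) + (1 − p) × 0 = p × (effect in affected men).

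The Background gives 73.9 % for men in their seventh decade, close to the trial's age range, and 62.9 % for men over 50.
- p = 0.739: 1 − 0.739 = 0.261, and 0.261 × 50 ≈ 13 men per arm without BPH. The mean effect is 74 % of that in affected men.
- p = 0.629: 63 %.
- p = 0.50 (assumed): 50 %.

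**4. What this could do to power.** Suppose that d = 0.626 were the IPSS effect in affected men, with SD fixed at 1. The protocol does not say this; it is an assumption. With 40 evaluable men per group:
- pooled comparison: power = Φ(p × 0.626 × √(40/2) − 1.960)
- symptomatic stratum only, 40p men per group: power = Φ(0.626 × √(40p/2) − 1.960)

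| p | Diluted d | Pooled power | Stratum size per group | Stratum power |
|---|---|---|---|---|
| 1 | 0.626 | 80 % | 40 | 80 % |
| 0.739 | 0.463 | 54 % | 29.6 | 67 % |
| 0.629 | 0.394 | 42 % | 25.2 | 60 % |
| 0.50 | 0.313 | 29 % | 20 | 51 % |

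Under these assumptions the stratum comparison falls short of 80 %, but it loses less than the pooled one.

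**5. Prevention.** None of the primary or secondary outcomes under Study outcomes counts new BPH. All are changes in volume, scores or hormone levels.

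**The case against.** The strongest reply is that the mixed population is the intended one. The Abstract speaks of older men, and the Background and Discussion name men with and without BPH. That stands: the absence of a symptom threshold is not an error, and requiring one would change the question.

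Second, the sample size was expanded for prostate volume, which has no symptom floor. That also stands, and it means the power figures above cannot be read as the trial's power.

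Third, BPH status is not an IPSS score. No baseline IPSS distribution is given, and the 73.9 % figure suggests that most men of this age have BPH. The direction of selection is open as well: leaving out treated men and asking for apparent health may lower the symptomatic share, while volunteers for a prostate study may have more symptoms than average. So the size is unknown.

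Fourth, the Discussion states a hope, not a decision rule; baseline IPSS and volume are collected; and a subgroup analysis may sit in an analysis plan that is not shown. A reader might infer that many entrants will have nothing to improve, or that the trial cannot support any treatment conclusion. The documents support neither. Affected men can be identified from the baseline data.

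What remains is that the stated design gives baseline status no role while the stated aims include therapy for men with BPH. A later subgroup analysis would not supply balanced allocation within strata, and its weight depends on its having been fixed in advance.

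**Conclusion.** The point holds as a gap between design and intended conclusion. Two of the three primary outcomes have a floor, the planning trial was in BPH patients, and nothing stated separates men with symptoms from men without. The pooled IPSS and Qol effects may be diluted by an amount the protocol does not let one determine.

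The figure of about 74 % of the effect in affected men rests on two assumptions: that 73.9 % applies to the enrolled men, and that those without BPH show no improvement. The power range from 54 % down to 29 % further assumes that the back-calculated 0.626 applies to IPSS. All of this is illustrative, and none of it applies to prostate volume.

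A pooled result would not by itself support a statement about treating BPH. A prevention statement has no outcome behind it.

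**What to change.** Keep the mixed population and make these changes.

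1. **Recruitment and Randomization:** measure IPSS before allocation and stratify randomisation by it, for example below 8 versus 8 or more. That cut-off is a proposal and does not appear in the protocol.
2. **Statistical analysis:** include baseline IPSS in the IPSS and Qol models, and pre-specify the IPSS and Qol comparison in the symptomatic stratum as the basis for any treatment statement.
3. **Discussion:** describe pooled results as effects on prostate volume and urinary symptoms in older men, and drop the prevention conclusion.
4. **Sample size:** state that the stratum comparison has lower power than the planned 80 %, and give the expected range.

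An IPSS entry threshold is optional. It would concentrate the sample but require more screening and narrow the question.

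The cost is mostly wording and the order of procedures, since IPSS is already a baseline measure. The real price is that the treatment statement rests on fewer men, for example about 30 evaluable per group instead of 40 if 73.9 % were symptomatic.

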### Inclusion criteria

Participants are required to meet all the following criteria:Aged between 60 and 70 yearsA relatively stable body weight over the past 6 months with a weight change of less than 2 %A sedentary lifestyle, not having exercised for the past 3 months, or exercising occasionally less than once a week for 20 min each timeNo Yi Jin Jing and/or Tai Chi training experience for the past 3 monthsApparently healthy, free of cardiovascular disease, and not being treated with BPH drugs or other therapies during the last 6 monthsVoluntary participation in this research for at least 6 months and provision of written informed consent

### Exclusion criteria

Subjects are excluded for any of the following:Signs and symptoms of or having the following diseases (but not limited to these diseases): Crohn’s disease, sarcoidosis, chronic diarrhea, heart disease, rheumatoid arthritis, systemic lupus erythematosus, and cancerHaving taken any relevant drugs in the last 6 months, such as for insulin-dependent diabetes mellitus or antibioticsAny conflict with the objectives of this study

### Randomization

After providing written informed consent, eligible participate will be randomly assigned into a control or one of two intervention groups, which have equal numbers of subjects. The randomization procedure will be conducted by an independent statistician using a computerized randomization program. Participants and three principal researchers are aware of the study-group assignments. However, to minimize any potential bias, other study personnel, especially those performing the tests and outcome evaluators or adjudicators, will be blinded to the subjects’ intervention allocation.

### Intervention

The subjects in both intervention groups will undergo the Yi Jin Jing or Tai Chi exercise training, respectively, with 30-minute sessions five times a week for 6 months. The control group will keep their regular daily life in normal living conditions without any intervention and/or exercise training. After completing the 6-month treatment sessions, participants in the Yi Jin Jing and Tai Chi groups will be asked to continue with their exercises, while the control participants are encouraged to maintain their usual activities and life. The research team will monitor these participants twice a month with home calls until the 3-month follow-up evaluations. All exercise participants are asked to record their exercise behavior for the 3 months.

All measurements will be conducted for every participant at baseline 2 weeks prior to starting the intervention, after completing the intervention (by retaking the interview surveys and tests in the sixth month), and at the 3-month post-intervention follow-up. Fasting blood samples will be collected in the morning of the testing day. In particular, we will measure prostate volume by ultrasound at baseline, at the end of the 6-month intervention, and additionally at the 3-month post-intervention follow-up. The intervention will be closely supervised by a physician and study personnel to minimize the occurrences of any accident or injury.

